### Monitoring

#### Data monitoring and trial steering committee

An independent Data and Safety Monitoring Board (DSMB) is available to monitor the trial’s progress and the participant’s safety. The board will include a biostatistician, an oncologist, and a senior oncology nurse faculty member not directly associated with the study. At quarterly intervals throughout the project, the board receives a comprehensive report of data regarding (1) all causes of mortality and (2) morbidity (hospitalizations, emergency room visits, and injuries/problems resulting from exercises, such as delayed-onset muscle soreness (DOMS), any reports of falls or injuries resulting from exercise, the development of lymphedema in previously unaffected participants, and safety concerns associated with exercise. Additionally, the rate of recruitment refusal and subject attrition will be tracked and reported in these quarterly reviews. These parameters are differentially monitored between the intervention and control groups.

If members of the research team identify concerns or problems, they will be reported to the University’s Institutional Review Board (IRB) and NIH as indicated by the IRB. Annual progress reports to the IRB and NIH will include a summary of the DSMB’s activity findings and any adverse events regarding human subjects.

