### Relevant concomitant care permitted or prohibited during the trial

Participants in the attention control group agree not to begin a new exercise program or change their level of exercise during the study.

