#### Adverse event reporting

The risk to participants in this study is expected to be minimal. However, there is a small risk of falls in participants who experience gait and balance difficulties due to neuropathy resulting from taxane therapy. The study team advises safety precautions such as having a sturdy chair nearby and a person supervising the exercise to increase safety and minimize the risk of falls. Participants randomized to the exercise intervention may experience DOMS due to increased tension on muscle fibers during the first few exercise sessions. Exercise-related DOMS decreases with repeated stimuli and does not typically require medical attention. In addition, a breach of confidentiality is a potential risk. Study materials have unique study numbers and are kept secured in locked files to minimize the risk of a confidentiality breach.

Patients are interviewed at each visit for assessment and asked about any adverse events. Surveillance for adverse events (AEs) and other relevant clinical circumstances associated with study participation occur at in-person visits scheduled at 0 and 16 weeks using a standardized Adverse Event Record Form. Adverse event reporting is unmasked to the study statistician and Data Safety and Monitoring Board (DSMB). Any AE will be investigated immediately, assessed for relatedness and expectedness by the study PI, and reported in a timely fashion as required by the DSMB and University of South Florida IRB.

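### The DSMB's falls and injury line, read naturally, counts only exercise-caused events yet is compared by arm, so by itself it cannot show the net effect on falls

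*Protocol article*

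**What the plan says.** The section on data monitoring and the trial steering committee sets out what the DSMB receives each quarter. Some items carry no cause limit: "all causes of mortality and (2) morbidity (hospitalizations, emergency room visits", and new lymphedema. Others are tied to exercise: "injuries/problems resulting from exercises, such as delayed-onset muscle soreness (DOMS", then "any reports of falls or injuries resulting from exercise", then safety concerns linked to exercise. The section says of the whole list: "These parameters are differentially monitored between the intervention and control groups".

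The concomitant-care section says of the control arm: "Participants in the attention control group agree not to begin a new exercise program or change their level of exercise during the study". The adverse event section names falls as a risk and gives the disease as the reason: "there is a small risk of falls in participants who experience gait and balance difficulties due to neuropathy resulting from taxane therapy". The Abstract and the Background also link neuropathy to a raised risk of falling.

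The adverse event section describes a wider collection: "Patients are interviewed at each visit for assessment and asked about any adverse events". The schedule and instrument are "in-person visits scheduled at 0 and 16 weeks using a standardized Adverse Event Record Form". Relatedness is assessed by the principal investigator once an event is known, and adverse event reporting is unmasked to the study statistician and the DSMB.

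**The concern.** A by-arm comparison is informative when an event can be counted on equal terms in both arms. If a fall counts only when exercise caused it, the qualifying cause is supplied by the trial to one arm and not to the other. Falls due to neuropathy, which both arms have, drop out.

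The programme trains gait and balance in women prone to fall, so the useful safety question is its net effect on falls. An exercise-attributed count can mislead in both directions. A programme that prevents daily-life falls but causes a few during sessions would look worse than control. A programme that causes extra falls outside sessions could look clean if nobody attributed them to exercise.

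**Working it through.** The document states no fall rate, safety count or safety power, so there is no figure to reproduce. The main check is textual, and the arithmetic only illustrates it.

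**Reading the line.** The exercise qualifier may apply to falls and injuries alike, or to injuries only. The items just before it and at the end of the list are both tied to exercise, which favours the restricted reading. Against that, the lymphedema item in the same run has no cause limit, and the punctuation does not show where the exercise examples end. On the looser reading falls are complete, but injuries from ordinary falls are still left out. The two readings give the board different tables.

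**Who can contribute events.** The intervention arm is asked to exercise three days a week for 16 weeks. Controls get no study exercise but may keep their usual level, so their count would be low and not necessarily zero.

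**Illustration on the restricted reading.** Inputs:
- n = 312 / 2 = 156 per arm (1:1 allocation, from the protocol).
- Control proportion falling over 16 weeks, p = 10%, 20% or 30% (assumption).
- Risk ratio for any fall, RR = 0.7, 1.0 or 1.3 (assumption).
- Share of fallers labelled as exercise-caused: qT = 30% in the intervention arm, qC = 0 to 5% in controls (assumption).

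All fallers: n·p·RR (intervention) against n·p (control). Filtered line: n·p·RR·qT against n·p·qC.

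For p = 20%, controls have 156 × 0.20 = 31.2 fallers. At RR 0.7 the intervention arm has 31.2 × 0.7 = 21.8. The filtered line is 21.8 × 0.30, about 6.6, against at most 31.2 × 0.05, about 1.6.

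| p | RR | All fallers, intervention v control | Filtered line, intervention v control |
|---|---|---|---|
| 10% | 0.7 | 10.9 v 15.6 | 3.3 v 0 to 0.8 |
| 20% | 0.7 | 21.8 v 31.2 | 6.6 v 0 to 1.6 |
| 20% | 1.0 | 31.2 v 31.2 | 9.4 v 0 to 1.6 |
| 20% | 1.3 | 40.6 v 31.2 | 12.2 v 0 to 1.6 |
| 30% | 0.7 | 32.8 v 46.8 | 9.8 v 0 to 2.3 |

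The filtered ratio is RR × qT/qC. With qC = 5% it is 0.7 × 6 = 4.2 for a beneficial programme, 6.0 for a neutral one and 7.8 for a harmful one. At RR 0.7 the line points the right way only if qT is below 0.05 / 0.7, about 7%. In the opposite case, if the 40.6 fallers at RR 1.3 all fell in daily life and none was labelled, the line would read 0 against 0 to 1.6 despite 9.4 extra fallers.

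**What an all-cause count could show.** Power for two proportions at two-sided 5%, 156 per arm, is Φ[(d − 1.96·SE0)/SE1], where d is the difference in proportions, SE0 uses the pooled proportion and SE1 the separate ones. At p = 20% and RR 0.7, d = 0.06, SE0 = 0.0425 and SE1 = 0.0424, giving 0.29. At p = 10% and 30% it is 0.16 and 0.45.

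**The case against.** The strongest reply is that the adverse event section already covers this. It asks about any event with no limit by arm or cause, judges relatedness only afterwards, and is unmasked to the DSMB. A control woman who falls at home can therefore be recorded and reach the board. A reader might infer that the whole by-arm safety comparison cannot show harm or benefit. The documents do not support that: deaths, hospitalizations, emergency room visits and lymphedema are also unrestricted, so the defect lies in one line.

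Two other inferences go too far. One is that controls must have zero events; the concomitant-care wording lets them continue their existing exercise. The other is to attach a significance test to the line. The protocol plans none, falls are not a listed outcome, and the label itself tells the board that events were attributed. It is also fair that the qualifier is ambiguous, and that an all-cause comparison would usually leave the effect on falls unresolved.

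What remains is this. The adverse event section names falls as a risk but not as an event to ask about, and its scheduled surveillance is at weeks 0 and 16 only, so it leans on recall. The quarterly content that the protocol does spell out is still the filtered list. The point does not rest on detail left to a charter or full protocol, because the article states the list and its qualifier. Filtering also needs a judgement of cause, and the principal investigator who makes it is described as blinded; an all-cause count needs no such judgement.

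**Conclusion.** The point holds for the falls and injury line. On the more natural reading, that line is asymmetric between arms by construction and cannot by itself show whether the programme raises or lowers falls. On the looser reading, the asymmetry shrinks to injuries. All-cause falls may still reach the board through general adverse event reporting, but the protocol does not make that explicit.

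The size cannot be taken from the document. Under the assumed inputs, the line shows an excess in the intervention arm at all three risk ratios, including a 30% reduction in falls. The counts depend on the assumed fall rates and attribution shares; the asymmetry itself depends only on exercise being assigned to one arm.

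An all-cause comparison would have low power (about 0.16 to 0.45 for a 30% reduction), but its direction would not be biased by its definition. Imperfect recall at week 16 would remain.

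**What to change.** In the data monitoring section, state that all falls and all injuries, whatever the cause or setting, are reported to the DSMB by arm, in line with the any-event collection in the adverse event section. Record separately where each event happened (study session, laboratory assessment or daily life) and whether it was judged related to exercise. List muscle soreness and exercise-session events descriptively for the intervention arm.

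The cost is a wording change in the protocol and DSMB report, plus a setting field on the existing Adverse Event Record Form; relatedness is already assessed. The small downside is more minor events to record in both arms. The Trial status section gives 33 participants recruited out of 312, so 312 − 33 = 279 could still be followed under the clearer definition.

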#### Adverse event reporting

The risk to participants in this study is expected to be minimal. However, there is a small risk of falls in participants who experience gait and balance difficulties due to neuropathy resulting from taxane therapy. The study team advises safety precautions such as having a sturdy chair nearby and a person supervising the exercise to increase safety and minimize the risk of falls. Participants randomized to the exercise intervention may experience DOMS due to increased tension on muscle fibers during the first few exercise sessions. Exercise-related DOMS decreases with repeated stimuli and does not typically require medical attention. In addition, a breach of confidentiality is a potential risk. Study materials have unique study numbers and are kept secured in locked files to minimize the risk of a confidentiality breach.

Patients are interviewed at each visit for assessment and asked about any adverse events. Surveillance for adverse events (AEs) and other relevant clinical circumstances associated with study participation occur at in-person visits scheduled at 0 and 16 weeks using a standardized Adverse Event Record Form. Adverse event reporting is unmasked to the study statistician and Data Safety and Monitoring Board (DSMB). Any AE will be investigated immediately, assessed for relatedness and expectedness by the study PI, and reported in a timely fashion as required by the DSMB and University of South Florida IRB.

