## Methods/design

### Study design

A two-group, 16-week randomized clinical trial is designed to address persistent taxane-induced peripheral neuropathy in women treated for invasive breast cancer. The study design is a parallel, two-arm, randomized controlled trial with a 1:1 ratio between groups.

A sample of 312 women who completed taxane-based chemotherapy for breast cancer and have symptomatic neuropathy (≥ 3 on a neuropathy visual analog scale VAS) ≥ 6 months following completion of taxane-based chemotherapy will be recruited. Participants are randomized to either a Home-Based Physical Activity Intervention (B-HAPI) for persistent taxane-induced neuropathy or an educational attention control group. Assessment of gait, balance, strength of lower extremity muscles, neuropathy symptoms, and nerve conduction velocity will be collected at baseline (prior to randomization) and 16 weeks. The participant flow diagram is shown in Fig. 1. The protocol follows the Standard Protocol Items: Recommendations for Interventional Trials (SPIRIT) Figure (Fig. 2) and Checklist (Additional File 1) [16].

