#### Attention control protocol

Participants in the attention control group receive a journal to record their clinic appointments and standardized breast cancer survivorship education based upon information from the American Cancer Society. At each data collection encounter, the intervention research assistant discusses the information in each pamphlet, allowing time for questions related to the material. In addition, participants in the attention control group receive telephone calls every other week which entail a social visit and reminder of data collection/attention intervention appointments to equalize contact further.

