### Assignment of interventions: allocation and blinding

Randomization to study groups is achieved using a computer-generated random numbers list (REDCap software, Nashville, TN) by the study statistician. A sealed, consecutively numbered, opaque envelope containing the subject’s group assignment (Exercise Intervention or Educational Attention Control) is opened to reveal the participant’s study group assignment. The study statistician generates the allocation sequence. The project manager enrolls participants, and the research assistant assigns participants to intervention groups. It is not an open-label study. The PI, data collectors, and the principal statistician are blinded. The data collector is blinded to the study group assignment. There is no unblinding procedure. No blocking or stratification is used.

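### After randomization adverse events are formally asked about only once, at week 16, too sparse for the promised quarterly by-arm safety reports; the PI's blinding and relatedness role also need reconciling

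*Protocol article*

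**What the plan says.** Under Adverse event reporting the protocol article describes how events are elicited: "Patients are interviewed at each visit for assessment and asked about any adverse events". It then fixes when: "Surveillance for adverse events (AEs) and other relevant clinical circumstances associated with study participation occur at in-person visits scheduled at 0 and 16 weeks". A standard record form is used at those visits. Under Study design, the assessments "will be collected at baseline (prior to randomization) and 16 weeks", and Table 3 likewise lists randomization last at the baseline visit.

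Under Data monitoring and trial steering committee, the DSMB receives a report each quarter on deaths, hospitalizations, emergency visits, falls, injuries, delayed-onset muscle soreness, new lymphedema, refusals and attrition. Of these the article says: "These parameters are differentially monitored between the intervention and control groups".

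On judging events, Adverse event reporting has each one investigated at once and "assessed for relatedness and expectedness by the study PI". It names only the study statistician and the DSMB as unmasked to these reports. The section on allocation and blinding says: "The PI, data collectors, and the principal statistician are blinded". It adds that no procedure for unblinding exists.

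**The concern.** Falls are the main risk that the article names for women with impaired gait and balance who exercise at home. It also expects muscle soreness in the first few sessions, which is the part of the program furthest from the week 16 interview. A board that meets quarterly and compares arms needs dated events, collected in the same way in both arms, close to when they happen. A single recall interview at the end serves that purpose poorly. It depends on memory over as much as 16 weeks, and it misses anyone who has left, including anyone who left because of an injury.

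Whatever surfaces earlier must come through contact that differs by arm. Intervention participants are called to be coached on problems with the exercises and keep an exercise diary. Controls are called socially and reminded of appointments. The same fall may therefore be more likely to be mentioned in one arm than in the other.

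The relatedness question is separate. Here it is largely whether the event came from the exercises, and that is hard to answer without learning the arm.

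**Working it through.** The article gives no expected event count or reporting delay, so there is no figure of its own to reproduce. The check sets the sections side by side and adds simple timing arithmetic.

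**Inputs.** Inquiry at weeks 0 and 16 (Adverse event reporting); week 0 before randomization (Study design, Table 3); quarterly DSMB reports, taken as 13 weeks (Data monitoring); N = 312 with 20% attrition (Sample size); call schedules (Attention control protocol, Strategies to improve adherence, Table 3, Plans to promote participant retention).

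**1. Inquiries after randomization.** Two visits, one before randomization: 2 − 1 = 1. No section puts adverse event questions into the calls or the diary.

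**2. Delay for an event that is not volunteered.** Assumptions: event times are uniform over weeks 0 to 16, and the DSMB calendar is unrelated to each participant's start.
- Wait until asked: mean 16/2 = 8 weeks, maximum 16. An event at the end of week 1 waits 16 − 1 = 15 weeks, more than a 13-week quarter.
- Wait until it appears in a quarterly report: mean 8 + 13/2 = 14.5 weeks, maximum 16 + 13 = 29.
- Share missing the next quarterly report: 1 − 6.5/16 = 0.594, about 59%.

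**3. Participants never asked.** If attrition means no week 16 visit, 0.20 × 312 = 62.4, about 62 women.

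**4. Calls over 16 weeks.**

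| Section | Intervention | Control |
|---|---|---|
| Table 3 | 4 weekly + 12/2 = 10 | 16/2 = 8 |
| Plans to promote participant retention | 4 + 3 × 2 = 10, or 4 + 1 = 5 if bi-monthly means every two months | 4 |
| Attention control protocol | not given | 16/2 = 8 |
| Strategies to improve adherence | 16 if weekly throughout | not given |

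The contrast within one section is 10 to 8, or 10 to 4 (5 to 4 on the other reading). The control schedule conflicts between sections, and so does the intervention schedule.

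**5. Effect of asking at calls every two weeks in both arms.** The maximum wait falls from 16 to 2 weeks and the mean from 8 to 1. With a wait uniform on 0 to 2 weeks, the share missing the next quarterly report is 1/13 = 0.077, about 8%, against 59%.

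**6. PI role.** The PI is listed as blinded, is not listed as unmasked to event reports, has no unblinding route, and is the only person named to judge relatedness. No sentence says how the judgment is made under blinding.

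**The case against.** The strongest reply is that week 16 is only the scheduled in-person inquiry. The article promises immediate investigation of any event and timely reporting, most naturally from the moment staff learn of it, and it provides for problems noticed by the research team to be passed on. Both arms are called. This stands: the delays in steps 2 and 5 apply only to events that nobody volunteers. It does not restore a scheduled question, and the article states a schedule here, so this is not detail that was merely left to a fuller document.

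Several stronger readings are tempting and are not supported:

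- **That events do reach the DSMB late and unequally by arm.** No section says so. The visit schedule is identical in both arms, and the PI's blinding neither delays events nor creates a difference between arms. Unequal capture is a risk that comes from the differing calls and diary.
- **That the contrast in calls is 16 to 4.** This pairs a weekly-throughout reading of one section with the control figure of another. No section describes both arms that way.
- **That the exercise is wholly unsupervised.** Study staff are not present, but the article advises having someone watch and a chair at hand, and it rates the fall risk as small.
- **That the PI's two roles contradict each other outright.** Causality can be assessed blind. The roles are in tension and need explaining.
- **That assessor blinding is broken at week 16.** For controls, "At each data collection encounter, the intervention research assistant discusses the information in each pamphlet", a role named separately from the blinded data collector. The order of the visit and the identity of the event interviewer are operational details that an article may leave out.

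**Conclusion.** The point holds as a weakness of safety ascertainment that should be corrected. One scheduled inquiry after randomization, at week 16, does not fit quarterly by-arm monitoring. An event not volunteered waits up to 16 weeks to be asked about, 8 on average if events are spread evenly, and about 62 of 312 participants may have no scheduled inquiry at the planned attrition. These figures rest on uniform event times, a 13-week quarter, no spontaneous report, and attrition meaning a missed week 16 visit. Spontaneous reports would shorten the delays. Soreness concentrated in the first sessions would lengthen them.

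A difference in capture between arms is plausible, but its size cannot be computed from the article. The PI's blinding and relatedness role must be reconciled. Nothing here shows that the efficacy comparison is affected.

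**What to change.** 1. **Same form, same weeks, both arms.** Ask a short version of the Adverse Event Record Form at matched scheduled calls, with a dated question on any fall or injury regardless of cause. On the Table 3 schedule the eight two-weekly calls can be common to both arms. The two extra early intervention calls (10 − 8 = 2) should either not carry the form or be matched in controls. The callers should administer it: they must know the arm because call content differs. Keep the week 16 interview.
2. **One call schedule.** Reconcile Table 3, the attention control protocol, the adherence strategies and the retention plan, and say what bi-monthly means.
3. **Relatedness.** Either have a team member who already knows the allocation and does not assess outcomes make the judgment, or state that the PI is not blinded for adverse event review.

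**Cost.** A few minutes per call, somewhat more events to process, and an amendment approved by the IRB. The first item needs no new visits; the third may mean naming a reviewer whom the article does not identify. At the stated 33 recruited, 312 − 33 = 279 participants would be covered from the start. Introducing the form in both arms on one recorded date keeps ascertainment comparable between arms before and after the change.
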